## Abstract

**Background:**

Due to the physical dose distribution characteristic of “Bragg peak” and the biological effect as a kind of high linear energy transfer ray, heavy ion therapy has advantages over conventional photon therapy in both efficacy and safety. Based on the evidence that prostate cancer lesions before treatment are the most common sites of tumor residual or recurrence after treatment, simultaneous integrated boost radiation therapy for prostate cancer has been proven to have the advantage of improving efficacy without increasing toxicities.

**Methods:**

This study is a prospective phase II randomized controlled clinical trial evaluating the efficacy and safety of functional imaging-guided carbon ion irradiation with simultaneous integrated boost for localized prostate cancer. One hundred and forty patients with localized prostate cancer will be randomized into carbon ion radiotherapy group and simultaneous integrated boost carbon ion radiotherapy group at a 1:1 ratio. The primary endpoint is to compare the incidence of treatment-related grade 2 and higher acute toxicities between the two groups according to National Cancer Institute Common Terminology Criteria for Adverse Events (NCI-CTCAE) version 4.03. Secondary endpoints are late toxicities, biochemical relapse-free survival, overall survival, progression-free survival, and quality of life.

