## Methods/design

### Trial organization/coordination

This study is designed as an open-label, prospective, single-center, randomized two-armed (carbon ion radiotherapy vs. simultaneous integrated boost radiotherapy) study, primarily evaluating the differences in the severity and incidence of acute toxicity in patients with localized prostate cancer treated with carbon ion radiotherapy and simultaneous integrated boost carbon ion radiotherapy and further optimizing carbon ion therapy for prostate cancer. The rationale for this SIB approach is to provide a greater overall tumor-killing effect to prolong the biochemical recurrence-free survival without additional toxicity as compared with standard treatment. The two study arms are defined by different treatment strategy with arm A (carbon ion radiotherapy at 65.6 Gy in 16 fractions) and arm B (SIB carbon ion radiotherapy to the imaging-visible malignancy at 72Gy in 16 fractions). The flow chart of this phase II trial is illustrated in Fig. 1. The study carries out in Shanghai Proton and Heavy Ion Center (SPHIC) in China, and ethical consent was obtained from the ethics committee of SPHIC before trial initiation. The number of the ethics committee of SPHIC (Institutional Review Board) is 2006-62-03. All patients have written informed consent before inclusion in the trial.

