During irradiation, all patients are regularly assessed for acute toxicities of normal tissues at least once a week until they have subsided. The adverse events, grading, and correlation with radiotherapy are documented at each evaluation. Specific evaluation contents include weekly routine blood tests to observe the hematological toxicity, monthly liver function tests to observe the liver toxicity, weekly routine urine examination to observe the occurrence of hematuria and urinary tract infection, IPSS questionnaire to evaluate urinary system toxicity, and weekly routine stool examinations and occult blood examinations combined with the symptoms of intestinal toxicity to exclude radioactive enteritis. Patients are treated with combined endocrine therapy, either neoadjuvant endocrine therapy or concurrent endocrine therapy, depending on their grading. When necessary, a supportive medication is initiated or adapted. When patients experience treatment-related adverse events, appropriate medications will be given according to the severity of the disease. If patients have an unexpected injury during the clinical study, financial compensation will be made in accordance with Chinese laws and regulations. Additionally, quality of life is collected during and at the end of radiotherapy. Table 1 summarizes the schedule.

**Table 1 Tab1:** Schedule of the trial

	Before radiation	During radiation	At the end of radiation (the final day of radiation)	Follow-up after treatment						
		Every week		The first year				The second and third years	The fourth year	From the fifth year
				Weeks 4–6 (first time)	The 3rd month	The 6th month	The 12th month	Every 3 months	Every 6 months	Every year
**Written informed consent**	**√**									
**Medical history/physical examination**	**√**	**√**	**√**	**√**	**√**	**√**	**√**	**√**	**√**	**√**
**KPS, ECOG**	**√**	**√**	**√**	**√**	**√**	**√**	**√**	**√**	**√**	**√**
**Pathological diagnosis**	**√**									
**Inclusion and exclusion criteria**	**√**									
**Peripheral blood routine examination**	**√**	**√**^**a**^	**√**	**√**	**√**	**√**	**√**	**√**	**√**	**√**
**Serum chemistry**	**√**	**√**^**a**^	**√**	**√**	**√**	**√**	**√**	**√**	**√**	**√**
**Urine and stool routine examination**	**√**	**√**^**a**^	**√**	**√**^**a**^	**√**^**a**^	**√**^**a**^	**√**^**a**^	**√**^**a**^	**√**^**a**^	**√**^**a**^
**Levels of PSA, fPSA, testosterone, and NSE**	**√**		**√**	**√**	**√**	**√**	**√**	**√**	**√**	**√**

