### Duration of the study

The primary endpoint is to compare the treatment-induced grade 2 or greater acute toxicity between arm A and arm B. Seventy patients are planned to be enrolled in each arm, and 140 patients are enrolled in total.

It will take about 5 years to complete the enrollment of all patients and every patient should complete at least 3 months of follow-up work after radiotherapy. The study is expected to start in October 2020 and primarily be completed in July 2025.

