### Statistical analysis

The primary endpoint of the study is to observe the difference in acute toxicity in patients with localized prostate cancer who receive carbon ion radiotherapy and SIB carbon ion radiotherapy. All the patients will be randomly assigned to arm A and arm B in a ratio of 1:1. Assuming a type I error of 0.025 and type II error of 0.2, and under the assumption that the probability of no more than 2 degrees of acute GU and GI toxicities in arm A is 90% (Pc), and the probability of no more than 2 degrees of acute GU and GI toxicities in arm B is also 90% (Pt), with a non-inferiority margin of 0.15, we estimate that a sample size of 63 participants per arm will yield 80% power to show non-inferiority. However, anticipating a possible 10% dropout rate in each group, per arm *n* = 70 patients will be recruited into the study such that a total of *N* = 140 patients is required.

Statistical analysis will be performed using SPSS software (V20.0, SPSS Inc., Chicago, IL, USA). The Mann-Whitney *U* test will be used to compare the differences in acute and late toxicity between the two arms. The Kaplan-Meier method will be used to estimate the biochemical relapse-free survival, progression-free survival, and overall survival of the entire cohort. The association between each of the candidate prognostic factors with biochemical relapse-free survival, progression-free survival, and overall survival rates will be tested using the log-rank test. Multivariate analysis will be performed using the Cox regression model.

Analysis is planned on an intention-to-treat population (ITT), with all participants to be analyzed in the group to which they were randomized. We will make efforts to collect complete data for all participants and minimize missing data. If required, the missing data will be dealt with last observation carried forward method or multiple imputation.

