## Data collection and management

CRFs will be recorded by investigators and the research coordinator. CRFs will be stored and archived by investigators.

There are special personnel for regular follow-up and data entry, and the study site has a special database for data storage. All study-related information will be stored securely at the study site.

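### The primary toxicity endpoint is limited to treatment-related events in some sections and not in others; if events are filtered by attribution in this open-label trial, the non-inferiority error is not protected

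*Protocol article*

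**What the plan says.** Two places define the primary event through a causal judgement. The Abstract (Methods) has "The primary endpoint is to compare the incidence of treatment-related grade 2 and higher acute toxicities between the two groups", and Duration of the study has "The primary endpoint is to compare the treatment-induced grade 2 or greater acute toxicity between arm A and arm B". Evaluation of side effects likewise speaks of acute toxicities from treatment.

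Two places do not. Outcome measures gives the primary objective as the difference in acute toxicities. Statistical analysis bases the sample size on acute GU and GI toxicity ("the probability of no more than 2 degrees of acute GU and GI toxicities in arm A is 90% (Pc", with the same figure for arm B) and names a Mann-Whitney test for acute and late toxicity. Neither mentions relatedness.

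On how events are judged, Trial organization/coordination calls the trial "open-label, prospective, single-center". Patient assessments says "The adverse events, grading, and correlation with radiotherapy are documented at each evaluation". Data collection and management says "CRFs will be recorded by investigators and the research coordinator". No arm-blind assessor or adjudicator is described.

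The non-inferiority design rests on a margin of 0.15 and "Assuming a type I error of 0.025 and type II error of 0.2".

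**The concern.** Both arms receive the same carbon ion dose to the same clinical target volume and differ only in the boost. Randomization should therefore balance events with other causes, and a relatedness filter adds little to the between-arm contrast. What it adds is a judgement that may be made with the arm known. Other explanations can be at hand: Patient assessments describes combined endocrine therapy and weekly urine tests that look for urinary tract infection.

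In a superiority trial, lost events usually make success harder. Here the aim is to show that arm B is not worse by 15 percentage points or more, so each arm B event called unrelated moves the result towards success. At stake is whether a non-inferiority claim carries the planned 2.5% error. It also matters which event the 10% planning rate describes, because the sections disagree.

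**Working it through.** **Inputs from the protocol (Statistical analysis).** Success rate 90% in each arm, taken here as a 10% event rate; margin 0.15; type I error 0.025; power 0.80; 63 per arm, 70 after 10% dropout.

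**Reproducing the plan's figure.** n = (1.960 + 0.842)² × (0.9×0.1 + 0.9×0.1) / 0.15² = 7.849 × 0.18 / 0.0225 = 62.8, so 63 per arm; 63/0.9 = 70. Reading 0.025 as two-sided gives 77, so the plan's number matches a one-sided 0.025.

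**Assumptions not in the protocol.**
- Decision rule: non-inferiority is declared if (pB − pA) + 1.96 × SE < 0.15, with SE = √[pA(1−pA)/n + pB(1−pB)/n]. The article states no test against the margin.
- True event rates at the margin: 10% in arm A, 25% in arm B.
- A fraction f of true events is called unrelated.

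**One value by hand.** With f = 10% in arm B only, the observed arm B rate is 0.25 × 0.9 = 0.225. SE = √[(0.09 + 0.1744)/63] = 0.0648. The chance of declaring non-inferiority is Φ[(0.15 − 0.125)/0.0648 − 1.96] = Φ(−1.57) = 5.8%. Exact enumeration over two binomial arms of 63 gives 6.6%.

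**Probability of false non-inferiority, exact enumeration:**

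| f | Arm B only, n = 63 | Arm B only, n = 70 | Both arms equally, n = 63 |
|---|---|---|---|
| 0 | 2.9% | 2.9% | 2.9% |
| 5% | 4.4% | 4.5% | 3.8% |
| 10% | 6.6% | 6.8% | 5.0% |
| 20% | 13.6% | 14.3% | 8.5% |
| 30% | 25.2% | 26.9% | 14.2% |

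At the margin, arm B is expected to have 63 × 0.25 = 15.75 events, so f = 10% means about 1.6 patients. Equal discounting also inflates the error because the margin is absolute: at f = 20% the observed rates are 8% and 20%, and the difference shrinks from 15 to 12 points.

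**The opposite direction.** With true rates of 10% in both arms, a 20% relative over-attribution in arm B gives an observed 12% against 10%. Power falls from 81% to 66% (exact, n = 63).

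**Cost of counting all events.** If the all-event rate were 12% in both arms, SE = √(2 × 0.12 × 0.88/63) = 0.0579, and power = Φ(0.15/0.0579 − 1.96) = Φ(0.63) = about 74%.

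**The case against.** The strongest reply is that the article does not fix an attributed-only analysis. A reader might infer from the Abstract that the plan's only toxicity analysis counts related events, but the sample size and the named test in Statistical analysis carry no such qualifier. This stands: what the documents show is an inconsistency, and the inflation follows only if the filter is applied.

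A reader might also infer that an investigator who knows the arm makes each relatedness call. The article says that relatedness is documented and who records the CRFs, not who judges it or that the judgement screens endpoint events. The full protocol may say more. This too stands; the mechanism is an inference from the open-label design and those two statements.

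It is tempting to say that every patient is on endocrine therapy, so another cause is always available. Patient assessments makes endocrine therapy depend on grading, and an event ascribed to it might still count as treatment-related. The scheduled urine, stool and occult-blood tests and the IPSS also constrain the judgement.

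The bias could run the other way. Staff who expect harm from a boost may over-attribute in arm B, and that costs power rather than inflating error. The documents give no basis for either direction or for any fraction.

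Finally, grading itself may be unblinded, and an attribution-free analysis does not cure that. Withholding the arm from assessors looks like a simple addition, but nothing in the article shows it to be feasible without cost in an open-label single-centre trial with weekly on-site assessment.

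**Conclusion.** The point holds in a conditional form. The protocol limits the primary event to treatment-related toxicity in two places and leaves the limit out where the trial is sized and the comparison named. If the filter is applied, fewer than two reclassified arm B patients more than double the false non-inferiority rate (2.9% to 6.6% at f = 10%), and f = 30% takes it to 25.2%. Discounting that is the same in both arms still gives 5.0% to 14.2% over the same range of f.

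These figures rest on true rates placed at the margin, an assumed Wald rule and assumed fractions. They show how sensitive the error is to attribution; they do not predict that such bias will occur. This is a worthwhile, inexpensive improvement, not a defect that invalidates the design.

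**What to change.** 1. Reconcile the Abstract and Duration of the study with Outcome measures and Statistical analysis: state whether relatedness is part of the primary event, and whether the 10% planning rate refers to related events or to all acute GU/GI events.
2. Pre-specify the non-inferiority comparison, margin 0.15, on all acute GU/GI grade 2+ CTCAE events regardless of attribution, alongside the treatment-related version, over the same time window. Name the test or confidence limit that is set against the margin.
3. State that non-inferiority will be reported as not robust if only the attributed version meets the margin.

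The cost is one further analysis of data already recorded at each evaluation. The downside is some noise from non-radiation events. Power is also somewhat lower if the all-event rate exceeds 10% (about 74% at 12% in both arms with 63 per arm). If the 10% already means all such events, no planned power is lost. The change does not remove bias in unblinded grading.

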**Discussion:**

This study adopts functional imaging-guided simultaneous integrated boost of carbon ion radiotherapy for localized prostate cancer, aiming to evaluate the differences in the severity and incidence of acute toxicities in patients with localized prostate cancer treated with carbon ion radiotherapy and simultaneous integrated boost carbon ion radiotherapy, in order to optimize the carbon ion treatment strategy for localized prostate cancer.

**Trial registration:**

ClinicalTrials.gov NCT05010343. Retrospectively registered on 18 August 2021

## Background

Radiotherapy is one of the main strategies for localized prostate cancer. The accuracy of irradiation dose delivery to the target volume is closely related to the higher local control as well as the lower side effects, and a higher radiation dose to the target may further increase survival. Results from the dose-escalation photon study [1] indicated that a radiation dose greater than 76Gy could significantly improve the biochemical relapse-free survival in patients with localized prostate cancer and the dose greater than 76Gy or less than 76Gy may achieve different 10-year failure-free survival rates of 73% and 50%, respectively. From the National Comprehensive Cancer Network (NCCN) guidelines [2], the recommended photon irradiation dose for low-risk localized prostate cancer should be 75.6–79.2Gy, and at least 81Gy for intermediate/high-risk localized disease. Thus, increasing irradiation dose might be of great significance for improving the efficacy of prostate cancer.

Currently, localized prostate cancer is mainly irradiated with conventional photon beam. Although intensity-modulated radiation therapy (IMRT)/image-guided radiation therapy (IGRT) could get better dose conformity than 3-dimensional conformal radiation therapy (3DCRT), the irradiation dose was still limited due to the surrounding dose-limiting structures such as rectum and bladder; otherwise, it might lead to severe gastrointestinal (GI) and genitourinary (GU) toxicities, which affect the patients’ quality of life. In addition, from the perspective of fractionation dose, conventional fractionated radiotherapy of prostate cancer might not achieve the best therapeutic effect [3–5]. Actually, although long-term results of the M. D. Anderson randomized trial [1] demonstrated that dose-escalation of conventional photon radiotherapy did improve freedom from biochemical and clinical progression, the 10-year incidence of grade 2 or greater GI toxicity was higher in the high-dose arm than in the low-dose arm (26% vs 13%, *p* = 0.013), as was the incidence of grade 2 or greater GU toxicity (13% vs 8%). Similarly, despite improved clinical or biochemical failure-free survival in the Dutch Phase III trial [6], the 7-year rate of late grade 2 or greater GI toxicity was 35% in the 78Gy arm versus 25% in the 68Gy arm (*p* = 0.04). A meta-analysis [7] showed that high-dose radiotherapy (74–80 Gy) was associated with an increased risk (odds ratio 1.72) of late grade 2 or higher GI toxicity compared with conventional-dose radiotherapy (64–70.2 Gy). Consequently, a better radiotherapy strategy is eagerly wanted.

Carbon ion radiotherapy (CIRT) [8] is currently a novel and powerful tool for radiotherapy which could possess a narrow Bragg peak-like depth dose and a sharp gradient at depths near its distal penetration. The CIRT with intensity-modulated carbon-ion therapy (IMCT) delivery provides better dose conformity to the prostate compared to conventional radiotherapy. As a kind of high linear energy transfer (LET) ray, the relative biological effectiveness (RBE) of CIRT is substantially higher than that of photon and proton-based irradiation, and the RBE value is suggested to be 2–3-fold over photon, producing a more powerful tumor cytotoxicity than conventional radiotherapy. Due to its inspiring physical and biological advantages, CIRT has been gradually proceeded to treat several malignancies [9–12], such as head and neck carcinoma, soft tissue sarcoma, osteosarcoma, lung cancer, and liver cancer with reported satisfactory clinical efficacy. Compared with photon therapy, data published by Japan [13–17] recommended hypofractionated CIRT to be one of the best choices for localized prostate carcinoma, especially for intermediate- and high-risk prostate cancer, with improved 5- and 10-year progression-free survival rates and the favorable late GU/GI toxicities. Previous studies [3, 4, 18] also reported the low alpha/beta value of prostate cancer cell, suggesting that prostate cancer might be more suitable for hypofractionated radiotherapy.

For definitive irradiation of localized prostate cancer, the clinical target volume is mainly defined as the entire prostate and part of the seminal vesicle based on the different risk groups, with a uniform dose delivery. Numerous studies [19–21] have shown that either local recurrence or residual lesions mainly occurred in the primary visible site, and may be correlated with biochemical recurrence of prostate cancer after definitive radiotherapy. A meta-analysis [22] further suggested that every 1-Gy increase in irradiation dose may reduce the risk of biochemical relapse by approximately 1.8%. Based on a multicenter result [23] for multiple systemic tumors, the survival rate was significantly improved after an additional 10–20% dose boost to the radio-resistant site. Tomé et al. [24] set up a prognosis model to predict the efficacy of simultaneous integrated boost (SIB) radiation therapy for solid tumors and revealed that if a boost dose ratio of 1.20–1.30 was given to 60–80% of the tumor, the estimated tumor control probability (TCP) values would rise from 50% to 70%. Based on equivalent uniform dose, Kim et al. [25] compared expected local tumor control and normal tissue toxicities between SIB technique targeting high-risk recurrence area and homogeneous dose technique using voxel-based iso-TCP maps. They found that SIB was a more effective method than homogeneous dose technique, significantly improving local control rate without increasing the normal tissue complications. Dosimetric studies [26, 27] and clinical data [28, 29] on volumetric modulated arc therapy (VMAT) and IMRT technologies further proved that SIB technique of prostate cancer may not increase the irradiation dose and toxic reactions of rectal and bladder, which indicated that simultaneous integrated boost irradiation had the advantage of improving the treatment efficacy without increasing the side effects for prostate cancer. Thus, patients might benefit from the SIB technique for solid tumors with improved tumor control and limited normal tissue damage.

This is a randomized controlled phase II clinical trial, whose objective is to integrate SIB technique with carbon ion treatment for patients with localized prostate cancer and further assess its safety and efficacy.

## Methods/design

### Trial organization/coordination

This study is designed as an open-label, prospective, single-center, randomized two-armed (carbon ion radiotherapy vs. simultaneous integrated boost radiotherapy) study, primarily evaluating the differences in the severity and incidence of acute toxicity in patients with localized prostate cancer treated with carbon ion radiotherapy and simultaneous integrated boost carbon ion radiotherapy and further optimizing carbon ion therapy for prostate cancer. The rationale for this SIB approach is to provide a greater overall tumor-killing effect to prolong the biochemical recurrence-free survival without additional toxicity as compared with standard treatment. The two study arms are defined by different treatment strategy with arm A (carbon ion radiotherapy at 65.6 Gy in 16 fractions) and arm B (SIB carbon ion radiotherapy to the imaging-visible malignancy at 72Gy in 16 fractions). The flow chart of this phase II trial is illustrated in Fig. 1. The study carries out in Shanghai Proton and Heavy Ion Center (SPHIC) in China, and ethical consent was obtained from the ethics committee of SPHIC before trial initiation. The number of the ethics committee of SPHIC (Institutional Review Board) is 2006-62-03. All patients have written informed consent before inclusion in the trial.

